**Figure 6. F6:**
[figure not shown]
Autoregressive cross-lagged panel model to investigate prospective effects (**A**) of LC-NE functioning on psychopathology (PSY). b and c: autoregressive effects; e2i, e3i, e4i, and e5i: time-specific measurement errors; LC: locus coeruleus; PSY: psychopathology.

##### Experimental Design

The study uses an accelerated longitudinal design with 3 assessment waves and time points: the baseline or initial assessment as part of Task 2.2 (T1; aged 4‐6 years), a 1-year follow-up (T2; aged 5‐7 years), and a 2-year follow-up (T3; aged 6‐8 years). At each time point, we assess neurophysiological (pupillometry), behavioral, and cognitive measures.

##### Neurophysiological Measures

At each time point, the validated pupillometric battery, as described in Objective 1, will be used to assess BPS and SEPR across multiple tasks.

##### Cognitive Measure

To assess the verbal and cognitive abilities, we will conduct 2 subtests from the WPPSI [93].

##### Behavioral Measures

At each timepoint assessment of the behavioral measures, as described in Task 2.2, will include caregiver questionnaires (CBCL 4‐18) and the multiple-source assessment of childhood adversity (see Table 1).

##### Statistical Analysis Plan

The accelerated longitudinal design allows estimation of an autoregressive cross-lagged panel model that will quantify the effect of previous LC-NE functioning (BPS and SEPR) on later transdiagnostic psychopathology factors (CBCL) across the age of 4-8 years (see Figure 6). We will control for potential cohort effects (initial age: 4 vs 5 vs 6 years) by including cohort as a random intercept. Each model fit will be evaluated by the predefined indices of CFI, TLI, RMSEA, and SRMR.

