**Methods:**

LOCUS-MENTAL includes 4 work packages. The centerpiece is an accelerated longitudinal study, in which a cohort of 300 preschool-aged children (aged 4‐6 years) will be recruited and followed up across 3 assessment waves, each one year apart. This will characterize developmental trajectories from 4 to 8 years of age. The primary outcome is the prediction of transdiagnostic psychopathology by pupillometry-derived LC-NE functioning. Transdiagnostic psychopathology is assessed by the Child Behavior Checklist (CBCL), while LC-NE functioning is assessed with pupillometry that includes core metrics of baseline pupil size (BPS) and stimulus-evoked pupillary response (SEPR). Cross-lagged panel models will be applied to the longitudinal data for quantifying causal effects between LC-NE functioning, childhood adversity, and psychopathology. Normative modeling and classification approaches will estimate an individual risk prediction based on pupillometric metrics of LC-NE functioning. The pupillometric battery has 4 passive auditory and visual paradigms. This battery will be validated with a multitrait-multimethod design that combines pupillometry with neurophysiological measures in electroencephalography, behavioral and cognitive measures, and neurocognitive paradigms. The study was approved by the Ethics Committee of the Faculty of Medicine at Goethe University Hospital (2024‐2160). Written informed consent will be obtained from caregivers and verbal assent by the children.

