### Sample Size and Power

Sample sizes (n) were determined based on recruitment feasibility and the ability to detect moderate effects with a power of *β*>.80. For each task, we estimated the power by Monte Carlo simulations (k=1000) within respective models [97,98]. In the following sections, the sample size and power are reported, respectively, for each specific objective or task.

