##### Sample Size and Power

For the core longitudinal study with a cross-lagged panel model, power is *β*=.82 for 300 participants to detect a moderate cross-lagged effect of LC-NE functioning on psychopathology (a=0.2; see Figure 6).

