##### Risk Assessment

A major risk is a low retention rate. A meta-analysis identified a mean retention rate of 73.5% and identified strategies to increase it [102]. This includes barrier reduction by including remote data collection (eg, offer data collection via phone and online), tracing strategies by locator documents with contact information, and community-building by sending participants thank-you, birthday, and holiday cards. We will implement these strategies in LOCUS-MENTAL to maximize our retention rate while maintaining ethical standards.

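### A random intercept for a three-level cohort adjusts the core cross-lagged model only partly for age at entry; fixed cohort indicators (or age) would do it at almost no cost

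*Protocol article*

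**What the plan says.** Task 3.1, Experimental Design: "The study uses an accelerated longitudinal design with 3 assessment waves and time points". Children enter at age 4, 5 or 6 and are seen three times, one year apart.

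Task 3.1, Statistical Analysis Plan: "The accelerated longitudinal design allows estimation of an autoregressive cross-lagged panel model", relating earlier BPS and SEPR to later CBCL factors. On age at entry it says: "We will control for potential cohort effects (initial age: 4 vs 5 vs 6 years) by including cohort as a random intercept".

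This model carries the main question. The Abstract (Methods) says: "The primary outcome is the prediction of transdiagnostic psychopathology by pupillometry-derived LC-NE functioning". Task 3.1, Sample Size and Power, gives a power of 0.82 "for 300 participants to detect a moderate cross-lagged effect of LC-NE functioning on psychopathology" ("a=0.2; see Figure 6").

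No other control for age is named for Task 3.1. The covariates to be explored there are adversity, previous psychopathology and clinical support, and the autoregressive paths adjust for earlier levels of each construct. Age is a named covariate only in Task 2.1.

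**The concern.** A random intercept suits many exchangeable clusters whose spread is to be estimated. Initial ages 4, 5 and 6 are three ordered groups fixed by the design. Their variance is estimated from three cohort means, and that estimate decides how strongly the model adjusts. When it is near zero, the cohort means are pooled and little adjustment takes place. When it is large, the result is close to a fixed-effect adjustment.

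Age is a plausible common cause of pupil measures and symptom level. If both differ by age at entry, part of that difference enters the path from LC-NE to later CBCL, which is the path that the study is built to estimate.

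**Working it through.** **Inputs from the article.** Three cohorts; 300 children; cross-lagged path 0.2; power 0.82 by simulation; retention benchmark 73.5%.

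**Assumptions (not in the article).** 100 children per cohort; linear cohort shifts per year of age; autoregression 0.5; correlation of 0.3 between earlier LC-NE and earlier CBCL; one lag with observed variables; two-sided alpha 0.05.

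**1. The stated power.** The article says "we estimated the power by Monte Carlo simulations (k=1000) within respective models" but does not give the simulation inputs. A normal approximation is power = Φ(0.2/SE − 1.96), with SE = √[(1 − R²)/((1 − ρ²)N)]. For N = 300, ρ = 0.5 and R² = 0.04, SE = √(0.96/225) = 0.0653 and power = Φ(1.10) = 0.865. Other settings (ρ 0 to 0.5, R² 0.04 to 0.5) reach up to 0.998. A value near 0.82 appears only with an added assumption. One is reliability 0.7 for one variable (0.826). Another is about 220 children (0.735 × 300), ρ = 0.3 and R² = 0.04 (0.823). The stated 0.82 can be neither confirmed nor refuted, and the point does not depend on it.

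**2. Precision of the cohort SD.** With 3 − 1 = 2 df, the chi-square 2.5% and 97.5% points are 0.0506 and 7.378. The limits for the SD are √(2/7.378) = 0.52 and √(2/0.0506) = 6.28 times the estimate.

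**3. How often the variance is set to zero.** In a balanced one-way layout the REML estimate is zero when the between-cohort F is at most 1. For fixed shifts of d SD per year, F has 2 and 297 df and noncentrality 100 × (d² + 0 + d²) = 200d².

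| d per year | noncentrality | P(variance = 0) |
|---|---|---|
| 0.1 | 2 | 0.345 |
| 0.2 | 8 | 0.047 |
| 0.3 | 18 | 0.0012 |

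**4. Identification in the structural model.** Two constructs at three waves give six variables. An unrestricted between-cohort covariance matrix has 6 × 7/2 = 21 elements. Three cohorts give a between-cohort matrix of rank at most 2, so such a set of random intercepts is not identified. A restricted version, such as one variance per equation, can be fitted but meets the imprecision in step 2.

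**5. Effect on the path.** Simulated model: CBCL at the next wave = 0.2 × LC-NE + 0.5 × earlier CBCL + cohort shift + error (2,500 runs per row). Bias is measured against the fixed-indicator estimate, which averaged 0.198 to 0.202.

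| LC-NE shift | CBCL shift | Bias, no cohort term | Bias, random intercept | Share left |
|---|---|---|---|---|
| 0.3 | 0.05 | 0.010 | 0.006 | 56% |
| 0.3 | 0.1 | 0.019 | 0.008 | 43% |
| 0.3 | 0.2 | 0.033 | 0.006 | 18% |
| 0.3 | 0.3 | 0.042 | 0.003 | 8% |
| 0.5 | 0.05 | 0.016 | 0.010 | 61% |
| 0.5 | 0.1 | 0.030 | 0.014 | 45% |
| 0.5 | 0.2 | 0.056 | 0.011 | 19% |
| 0.5 | 0.3 | 0.077 | 0.007 | 9% |

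Repeat runs put the upper end of the random-intercept bias at about 0.016, so the range is about 0.003 to 0.016, at most 0.016/0.2 = 8% of the path.

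**6. Error rates.** In 1,500 runs per setting, type I error where cohort shifts both variables was 0.051 to 0.067 with the random intercept. With fixed indicators it was 0.042 to 0.059 over all settings. Power in this simplified model was 0.979 to 0.994 and 0.975 to 0.987 respectively.

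**The case against.** The strongest reply is that the problem largely limits itself. The variance is often zero only when cohort effects on the outcome are weak, and then there is little to remove. When they are strong, the random intercept removes about 80 to 90% of the confounding. Type I error is barely raised and power is nearly the same under either specification. The shifts are assumed. CBCL is analysed as T-scores, which are referenced to norms, and the autoregressive paths already absorb earlier levels; both could reduce what is left. All of this stands, and it sets the weight of the point.

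Four stronger readings are tempting but not supported:

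- A reader might infer that the variance cannot be estimated at all. It can, with the limits in step 2. Non-identification applies to an unrestricted set of random intercepts, which the article does not specify.
- A reader might expect the variance to be zero in about 18% and 9% of datasets at a cohort SD of 0.2 and 0.3. Those rates arise if cohort effects are drawn at random from a normal distribution: P(F ≤ 1/(1 + 100 × SD²)) = 0.18 and 0.10. For fixed, ordered ages the rates in step 3 apply.
- A reader might infer that the model will fail to converge. No cross-lagged structural model was fitted here, and the article does not name a multilevel one. Its paragraph on missing data mentions both mixed models and structural equation models for this work package.
- A reader might infer that equality of the lagged paths across ages will go untested. The article neither claims nor excludes such a test, and a full analysis plan may contain it. It is not part of the error.

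**Conclusion.** The point holds as a should-fix. The article commits its core model to an adjustment that does not suit three design-fixed groups, and names no other control for age at entry there. Followed as written, the adjustment is incomplete to a degree that depends on a variance estimated from 2 df. The likely size is small: about 0.003 to 0.016 on a path of 0.2. This rests on equal cohorts of 100, linear shifts of 0.3 to 0.5 SD per year in LC-NE and mainly 0.05 to 0.2 in CBCL, and a single-lag model with observed variables. The bias is upward when both shifts have the same sign, as assumed here, and would be downward if they differ. Nothing here shows that the study's conclusion would change. The case for acting is that the better specification is simple, costs almost nothing, and can be fixed before the data are analysed.

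**What to change.** In Task 3.1, Statistical Analysis Plan, replace the random intercept with two fixed cohort indicators (age 5 and age 6 against age 4), or with exact age at T1, as predictors of LC-NE and of CBCL at every wave. State which of the two is primary.

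The cost is one sentence and two degrees of freedom per equation (one for linear age). In the simulation this left power almost unchanged. If retention is near the cited benchmark ("A meta-analysis identified a mean retention rate of 73.5"%), about 220 children remain and two degrees of freedom are still negligible.

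A three-group comparison of the autoregressive and cross-lagged paths is an optional sensitivity check.

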##### Expected Outcome and Study Hypotheses

This core of LOCUS-MENTAL will be informed by the outcome of task 2.2. We expect (see Figure 1) that higher BPS as an index of LC-NE tonic activity predicts a higher p-factor. Increased and decreased SEPR as an index of LC-NE phasic activity is expected to predict higher internalizing and externalizing symptoms, respectively. This would predict future psychopathology based on pupillometric markers. The stability of the investigated constructs is controlled for by autoregressive effects. The structural equation models will be explored for the covariate effects of childhood adversity, previous psychopathology, and received clinical support (eg, in the context of the outpatient clinic for early detection).

##### Risk Assessment

A major risk is a low retention rate. A meta-analysis identified a mean retention rate of 73.5% and identified strategies to increase it [102]. This includes barrier reduction by including remote data collection (eg, offer data collection via phone and online), tracing strategies by locator documents with contact information, and community-building by sending participants thank-you, birthday, and holiday cards. We will implement these strategies in LOCUS-MENTAL to maximize our retention rate while maintaining ethical standards.

### Task 3.2: LC-NE Functioning Mediates the Effect of Stress Responses on the Development of Transdiagnostic Psychopathology

#### Participants

Participants in this study will comprise a subsample of 5‐6-year-olds (n=160) at one randomly selected timepoint (T2 or T3) from the large longitudinal cohort (Task 3.1).

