**Figure 4. F4:**
[figure not shown]
LOCUS-MENTAL study design with task integration. The flowchart illustrates the longitudinal study design consisting of a pilot phase and 3 primary assessment waves (**T1, T2, AND T3**) each one year apart. Each assessment wave spans over 2 years. The longitudinal study will follow a cohort of 300 preschool children (initially aged 4‐6 years). Dark blue boxes indicate longitudinal study elements, and light blue boxes indicate cross-sectional tasks within the longitudinal study. Dotted lines indicate selection of a specific subsample at specific time points, including a randomized subsample (n=160) either from T2 or T3 for Task 3.2. Small “n” represents the subsample number, while “N” represents the primary study sample.

**Table 1. T1:** Assessment measures and questionnaires of LOCUS-MENTAL.

Modality, instrument and task		Construct	Objective
Questionnaires (caregiver)	
core set		Demographic data	1.1.‐3.2
CBCL^a^ [4-18,82]		Psychopathology	2.1‐3.2
BIQ^b^ [83]		Behavioral inhibition	2.1‐3.2
ARI^c^ [84]		Irritability	2.1‐3.2
CBQ-VSF^d^ [85]		Temperament	2.1‐3.2
ACE+^e^ [86]		Childhood Adversity	2.2‐3.2
F-SoZu 6^f^ [87]		Social support	2.2‐3.2
Interview (child)	
CLES-P^g^ [88]		Childhood adversity	2.2‐3.2
VEX-Preschool^h^ [89]		Violence exposure	2.2‐3.2
Pupillometry battery	
Auditory oddball [90]		LC-NE activity	1.1‐3.2
Visual oddball [91]		LC-NE activity	1.1‐3.2
Cued visual search [92]		LC-NE activity	1.1‐3.2
Rapid sound sequences [24]		LC-NE activity	1.1‐3.2
Cognitive tests	
WPPSI^i^ subtest–vocabulary [93]		Verbal IQ estimate	1.1‐3.2
WPPSI subtest–block design [93]		Nonverbal IQ estimate	1.1‐3.2
Bio samples	
Hair sample		Retrospective cortisol level	2.2‐3.2
Saliva sample		Acute cortisol level	2.2‐3.2
Assessment	
Child stress test [94]		Stress reaction	3.2
EEG^j^	
See pupillometry tasks		LC-NE activity	1.1‐2.1
Go/NoGo Task [50]		Error Related Negativity (ERN)	2.1
Neurocognitive tasks	
Dot-probe tasks [95]		Irritability	2.1
Frustrative reward learning task [96]		Irritability	2.1

a CBCL: Child Behavior Checklist

b BIQ: Behavioral Inhibition Questionnaire

c ARI: Affective Reactivity Index

d CBQ-VSF: Children’s Behavior Questionnaire–Very Short Form

e ACE+: Adverse Childhood Experiences Questionnaire Plus

f F-SoZu 6: Social Support Questionnaire

g CLES-P: Childhood Life Events Scale–Preschool

h VEX-Preschool: Violence Exposure Scale–Preschool

i WPPSI: Wechsler Preschool and Primary Scale of Intelligence

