### Work Package 3 (Objective 3): Prospective Effect of LC-NE Functioning in a Developmental Model of Vulnerability and Stress

#### Task 3.1: LC-NE Functioning Predicts Later Transdiagnostic Psychopathology.

##### Participants

The study will follow the sample of 300 preschool-aged children, initially assessed in Task 2.2 at 4‐6 years of age across 3 time points.

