#### Sample Size and Power

A power analysis using a bivariate latent growth curve model indicates a power of *β*=.82 for 160 participants to detect a moderate path coefficient (b=0.2) of cortisol reactivity on changes in psychopathology.

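### Task 3.2 allows the single stress test at T3, the last wave, where cortisol follows all observed change in psychopathology; its 5-6 age window also leaves little or no margin for 160 children

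*Protocol article*

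**What the plan says.** The Participants entry of Task 3.2 restricts the subsample to ages 5 to 6 and specifies "year-olds (n=160) at one randomly selected timepoint (T2 or T3) from the large longitudinal cohort (Task 3.1". The legend of Figure 4 describes the same group as "including a randomized subsample (n=160) either from T2 or T3 for Task 3.2".

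The parent cohort is set out under Task 3.1. Participants: "The study will follow the sample of 300 preschool-aged children, initially assessed in Task 2.2". Experimental Design gives the later waves as "a 1-year follow-up (T2; aged 5‐7 years), and a 2-year follow-up (T3; aged 6‐8 years", the third and last of three. The Statistical Analysis Plan of Task 3.1 refers to "cohort effects (initial age: 4 vs 5 vs 6 years", without giving the size of each entry cohort.

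On purpose, Objective 3 under Main Objectives has Task 3.2 linking stress responses measured early to psychopathology measured afterwards. The Task 3.2 power statement gives 0.82 with 160 participants for a "path coefficient (b=0.2) of cortisol reactivity on changes in psychopathology", in a bivariate latent growth curve model. The Experimental Design entry of the same task calls the endocrine measurement cross-sectional.

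**The concern.** Two parts of the design do not fit together.

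The first is time order. A path from cortisol reactivity to change in psychopathology has a prospective meaning only if some of that change is observed after the cortisol measurement. A child tested at T3 has no later wave.

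The second is the age window. A random choice between T2 and T3 requires the child to be 5 to 6 at both, and most of the cohort is not.

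At stake are the prospective mediation claim of Task 3.2 and the number of children who can support it.

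**Working it through.** **Time order.** CBCL is scheduled at T1, T2 and T3. For a T2-tested child, the change from T2 to T3 follows the stress test. For a T3-tested child, no change does. Table 1 lists hair and saliva samples for Objectives 2.2 to 3.2 but the child stress test for 3.2 only, so earlier samples cannot supply cortisol reactivity for T3-tested children. This step needs no assumption.

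**Age eligibility** (visits one year apart, as stated):
- Age-4 entrants are 5 at T2 and 6 at T3: eligible at both.
- Age-5 entrants are 6 and 7: eligible at T2 only.
- Age-6 entrants are 7 and 8: never eligible.

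**The plan's power figure.** The alpha, sidedness and growth parameters behind 0.82 are not given, so it cannot be reproduced exactly. As a proxy, treat b = 0.2 as a correlation: atanh(0.2) × √(160 − 3) = 0.2027 × 12.53 = 2.54. Power is Φ(2.54 − 1.645) = 0.815 one-sided and Φ(2.54 − 1.96) = 0.719 two-sided at 0.05. The one-sided match may be coincidence, and I do not call 0.82 wrong.

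**Supply.** Assumptions: entry cohorts n4 = n5 = n6 = 100. The protocol's only retention figure is a literature mean of 73.5% (Task 3.1, Risk Assessment). I apply it either at both waves, or at T3 with its square root, 85.7%, at T2. Let r2 and r3 be retention at T2 and T3.
- (a) 1:1 draw per child, tested only if aged 5 to 6: n4(r2 + r3)/2 + n5·r2/2
- (b) Draw only among waves at which the child is 5 to 6: n4(r2 + r3)/2 + n5·r2
- (c) All eligible children tested at T2: (n4 + n5)·r2
- (d) All tested at T3: n4·r3

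| Reading | No dropout | 85.7% at T2, 73.5% at T3 | 73.5% at both |
|---|---|---|---|
| (a) | 150 | 122.5 | 110 |
| (b) | 200 | 165 | 147 |
| (c) | 200 | 171 | 147 |
| (d) | 100 | 73.5 | 73.5 |

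Under (c), 160 needs r2 ≥ 160/200 = 80%.

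The cohort split matters. With 120/100/80 entrants aged 4/5/6, (a) gives 170 before dropout and 125 to 138 after it, and (c) gives 220, then 162 to 189. With 80/100/120, (a) gives 130, then 96 to 107, and (c) gives 180, then 132 to 154.

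**Children tested at T2 who also have a T3 score** (equal cohorts, r3 = 73.5%): (a) 100 × 0.735 = 73.5; (b) 150 × 0.735 = 110; (c) 200 × 0.735 = 147. Proxy power, one-sided / two-sided: n = 74, 0.53 / 0.40; n = 110, 0.67 / 0.56; n = 147, 0.785 / 0.68. These show direction only, because the proxy is not the planned growth model.

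**The case against.** A reader might infer from the age arithmetic that the cohort cannot supply 160 children. The documents do not support that. With equal cohorts about 200 children are 5 to 6 at T2, and the wording is compatible with drawing only among age-eligible children. The counts of 150 and below come from a literal coin flip per child, which the article does not spell out and which the full protocol may settle. Cohort sizes are not stated, and 73.5% is a literature mean quoted alongside measures to improve on it, not the study's own forecast. All of this stands, and it reduces the supply point to a thin margin.

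A reader might also infer a specific loss of power from 0.82. That is not established either, because the simulation inputs are not given. Leaving out age-6 entrants is not an error in itself, since it follows from a declared age restriction on a subsample.

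On time order, the defence is that the task calls its cortisol measurement cross-sectional, that its analysis section speaks of association, and that a growth model can still be fitted to T3-tested children. It can, but the path then describes change that has already happened. The cross-sectional label conflicts with the objective and the power statement and does not resolve them. The defence does limit the problem to the T3-tested share.

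**Conclusion.** The timing defect holds on the text alone: for children tested at T3, the powered path can only be a concurrent or retrospective association. The mismatch between the age window and the T2/T3 draw also holds by arithmetic, whatever the cohort sizes.

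The shortage of children is conditional. With equal cohorts and the retention range used here, 160 is missed under a literal 1:1 draw even before dropout. Under an age-eligible draw it lies between just met (165) and missed (147). No attrition allowance is stated for the 160, and the missing-data section excludes missing bio samples case-wise, which lowers the usable number further.

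The core Task 3.1 analysis of pupillometry and later psychopathology is not affected.

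**What to change.** Before T2 begins, specify that the stress test and cortisol sampling take place at T2 for all Task 3.2 children. The 5-6 window can stay; widening it is not needed to reach the pool in row (c). Relate T2 cortisol reactivity to T3 psychopathology, adjusting for T1 and T2 scores. Restate n and power for that analysis, with alpha and sidedness, and allow for attrition at T2 and T3 and for case-wise loss of bio samples. Bring Objective 3, the Figure 4 legend and the Participants, Power and Experimental Design entries of Task 3.2 into line.

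If T3 testing is kept, state how the wave is drawn given the age window, analyse the T3-tested children as a concurrent or retrospective association only, and report the prospective n and power separately.

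The cost is protocol wording and appointment planning, with no additional stress tests. The sessions concentrate in one wave, 160 still depends on T2 retention of at least 80% with equal cohorts, and the restated power may be lower than 0.82. The longitudinal study was scheduled to start in April 2026 with T2 a year after T1, so the change can be made before testing begins. A later outcome for children already assigned to T3 cannot be recovered afterwards.
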